**Methods/Design:**

This is a single-centre randomized controlled parallel group trial, in a British university hospital.Randomization is achieved using a website and computer-generated concealed tables. Participants are 80 patients 70 years or over with acute hip fracture undergoing operative repair. The intervention group receive three daily infusions of 200 mg iron sucrose, starting within 24 hours of admission. The control group receive standard hospital care at the discretion of the clinical team. Red cell transfusions for each group are given in accordance with standard clinical triggers. The primary outcome is an increase in mean reticulocyte count in the intervention group at day 7. Secondary outcome measures include haemoglobin concentrations, early and late transfusion rates, infectious and cardiovascular complications, mobility and 30-day mortality.

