**Discussion:**

This is a pilot study to demonstrate haematopoietic efficacy of intravenous iron in this setting. Hence, we have chosen to measure change in reticulocyte count rather than the more clinically relevant differences in haemoglobin concentration or transfusion rate. If our results are positive, the study will provide the necessary information for development of a full-scale trial of intravenous iron.

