Pre-existing anaemia on admission is further exacerbated by the effects of intravenous rehydration, and small but significant intra-operative blood loss results in between one-third and two-thirds of patients receiving blood transfusions within the first few days following operation [5]. The likelihood of transfusion is related to fracture type: subtrochanteric and trochanteric fractures have the highest transfusion rates in both anaemic and nonanaemic subjects. Poor nutrition in the postoperative period is also unlikely to replenish iron stores. Surgery itself may further induce a functional iron deficiency due to humoral suppression of erythropoiesis [12]. Functional iron deficiency does not respond well to oral iron, as iron stores may be normal, and this suppresses intestinal absorption of iron. Indeed, postoperative oral iron has been shown to be of no benefit and also has a high incidence of side effects [13]. Whereas blood transfusion improves [Hb], some authors have found an association between transfusion and improved mobility [5]; others have not found this association, but found that transfusion might reduce readmission rates [14]. Infection rates may also be increased with the use of blood transfusion [15] and there are significant financial constraints with the current cost of a unit of blood in the UK around £200. A recently reported North American trial assessed the effects of liberal versus restrictive postoperative transfusion strategies following hip fracture in patients with cardiovascular risk factors [16-18]. That study found no differences in self-reported mobility or death at 60 days, though there was an increase in cardiovascular complications in the restrictive group. It would seem therefore, at this time that anaemia is a poor prognostic factor but that red cell transfusion does not necessarily alter outcome.

Alternatives to blood transfusion include reduction in blood loss in the perioperative period; stimulation of erythropoiesis with erythropoietin; and oral or intravenous iron.

Pharmacological reduction of blood loss with tranexamic acid has been assessed recently [19]. Although there was a trend to reduced transfusion requirements and reduced postoperative infections, there was also a trend towards increased thrombotic events in the tranexamic acid group and it is therefore not a recommended therapy in this group, despite being advocated for patients with multiple traumas [20].

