
Intravenous iron therapy is relatively inexpensive; 200 mg of iron sucrose costs around £15. Administration costs for i.v. iron are likely to be similar to blood transfusion, in terms of consumables and nursing time. Even if the only benefit of intravenous iron is to reduce transfusion rates, the potential cost savings are considerable. Potential benefits, such as a reduction in infectious complications, which are suggested by the current literature, would result in significant cost savings to the healthcare economy, as well as improved quality of care. The direct consumable costs are probably slightly in favour of i.v. iron. With an estimated i.v. iron cost of £43 and blood unit cost of £200, assuming that an average of two units are transfused when given, if i.v. iron reduces transfusion rates from 38% to 25%, the direct cost saving in transfusion-related costs is around £10 per patient. Unlike cost savings from length of stay, these are direct savings to the healthcare system that can be realised, as well as releasing a scarce resource for use elsewhere.

The current literature supports the hypothesis that i.v. iron might be an effective and safe treatment, reducing the need for blood transfusion following hip fracture. Given the differences between UK and Spanish hip fracture management, particularly regarding time to operation, it is unclear whether the promising results from the Spanish experience will be applicable to the UK hip fracture population. It is unknown at present whether i.v. iron would have sufficient erythropoietic effect in hip fracture patients to reduce transfusion rates in the early postoperative period.

A large randomized controlled trial of preoperative i.v. iron for patients with hip fracture may be appropriate. To inform appropriate design of such a trial, a pilot study evaluating the haematological effect of i.v. iron in this population is required.

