### Statistics

Data will be analyzed by the research team in conjunction with a medical statistician, using the latest version of SPSS software. There will be no interim analysis.

The primary outcome measure, difference in mean reticulocyte count between groups in the full analysis set will be analyzed using unpaired *t* tests or Mann-Witney tests as appropriate. Differences between groups in maximal change in [Hb], serum transferrin concentration, postoperative mobility, number of units transfused and estimated costs will similarly be analyzed.

Risk ratios will be described for categorical data: the number of patients in each group with cardiovascular or infective complications; and the number of patients requiring transfusion. Descriptive statistics will be used to summarise length of stay and 30-day mortality.

Prespecified subgroup analysis will be undertaken according to admission haemoglobin concentrations ([Hb] <12 or >12 g/dl) and fracture type (sub-trochanteric, extracapsular, intracapsular, pathological).

In addition to the calculated values, confidence intervals and odds- ratios will be presented when appropriate. All clinical information including all adverse events will be presented in full. All secondary analyses will be interpreted with caution as the sample size calculation is based on the primary outcomes only. However, the level of power associated with secondary results will be investigated.

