### Sample size and justification

We propose to study a convenient sample size, with 40 participants in each group. Groups of 35 participants each would provide a statistical power of 80% for finding an absolute difference in maximum reticulocyte count of 1%, assuming a standard deviation of approximately 1.6%. This would also provide a statistical power of 80% for finding a difference in serum transferrin receptor concentration of 0.33 mg/dl. This is a conservative estimate of effect size; Garcia-Erce et al. [25] found differences of 1.75% and 0.4 mg/dl respectively. The extra ten patients are included to account for drop-outs.

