
It is unlikely that intravenous iron, as a single intervention, will alter major outcomes, such as length of stay, mortality or readmission rates to a clinically significant degree, but it is plausible for it to have a beneficial effect on transfusion rates. However, this is only likely to happen if a significant effect on erythropoiesis occurs; hence, our choice of the absolute difference in reticulocyte count as the primary outcome of this study. We have chosen day seven as the primary time point for measuring difference in reticulocyte count. Although an effect may be seen at later times, we believe, consistent with the literature [25], that if a clinically significant effect is present, it will be observed within one week. Prolonging the observation time also risks losing participants due to discharge.

If the results of this study are positive, it will provide the necessary information for development of a full-scale trial of intravenous iron. There is an increasing awareness of the benefit of bundles of care [34] as opposed to single ‘magic bullet’ interventions [35] to improve outcomes following surgery. A full-scale trial would help to define the potential cost, resource requirement (blood products) or direct patient benefit of using intravenous iron as part of such a bundle of care. If there is a cost benefit to using intravenous iron, this could be significant: around 80,000 patients have operative fixation of hip fracture in the UK each year [36]. Conversely, if there is no benefit in the UK setting, then healthcare resources could usefully be directed elsewhere.

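### The primary reticulocyte 'count' has no stated unit and is powered as a percentage, which donor red cells lower; a difference between arms can therefore, to a small extent, reflect transfusion rather than erythropoiesis

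*Protocol article*

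**What the plan says.** The outcome is named as a count, without a unit, wherever it is defined:

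- Abstract, Methods/Design: "The primary outcome is an increase in mean reticulocyte count in the intervention group at day 7".
- Statistics: "The primary outcome measure, difference in mean reticulocyte count between groups in the full analysis set", to be compared by an unpaired t test or a Mann-Whitney test.
- Discussion: "our choice of the absolute difference in reticulocyte count as the primary outcome of this study".
- The primary aim also speaks only of an increase in reticulocyte count.

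The sample size section alone gives a scale. It refers to "finding an absolute difference in maximum reticulocyte count of 1%, assuming a standard deviation of approximately 1.6" per cent, and compares this with a difference of 1.75% in the cited parallel-group study.

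On transfusion, the Background describes "between one-third and two-thirds of patients receiving blood transfusions within the first few days following operation". Its cost paragraph works through the case "if i.v. iron reduces transfusion rates from 38% to 25" per cent, with two units per transfused patient. The full analysis set is everyone with an initial and a day-7 reticulocyte count, whether transfused or not.

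The abstract states the purpose: "This is a pilot study to demonstrate haematopoietic efficacy of intravenous iron in this setting".

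**The concern.** A reticulocyte figure in per cent is naturally read as reticulocytes divided by all red cells. The document does not say so, but gives no other scale. Transfused cells enter the denominator. If they bring few reticulocytes, a transfused patient's percentage falls although red cell production is unchanged.

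Most of the transfusions described would come before the day-7 sample. If controls are transfused more often than patients on iron, the control mean is pulled down and the comparison moves towards iron. The primary analysis is an unadjusted two-group test, and the article says nothing on how transfusion bears on it.

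Two things are at stake. The trial wants to conclude that iron stimulates erythropoiesis, and a percentage alone cannot separate more reticulocytes from fewer donor cells. Also, the named outcome could be analysed as a percentage or as cells per litre, and the stated power applies only to the percentage.

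**Working it through.** **The plan's own figure.** The inputs are a difference of 1 point, an SD of 1.6 and 35 per group. Alpha is not stated, so two-sided 0.05 is assumed.

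- Standard error of the difference: 1.6 × √(2/35) = 0.382 points.
- Power at 35 per group: 74.4% by the normal approximation, 73.2% by the noncentral t. The document says 80%.
- 80% power needs 41 per group by the normal approximation (42 by the t).

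The shortfall is a separate matter. It is noted here because the stated 80% should not be taken as established even for the percentage.

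**Inputs for the transfusion effect.**

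| Input | Value | Source |
|---|---|---|
| Units per transfused patient | 2 | Background, cost paragraph |
| Transfused, control vs iron | 38% vs 25% | Background, cost illustration |
| Transfused, control vs iron | 70% vs 24% | Background, cited parallel-group study (non-randomized) |
| Transfused, control vs iron | no difference | Background, cited randomized trial |
| Day-7 percentage without transfusion, R | 2.5 to 4.5 | Assumption |
| Rise in red cells per unit, g | 7 to 10% | Assumption |
| Reticulocytes in donor blood | negligible | Assumption |

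**Loss in a transfused patient** = R × (1 − 1/(1 + 2g)).

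- Low end: 2.5 × (1 − 1/1.14) = 0.31 points.
- High end: 4.5 × (1 − 1/1.20) = 0.75 points.

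**Shift in the arm difference** = loss × (proportion transfused on control − proportion transfused on iron). The last column is the chance of a significant result favouring iron when production is equal in both arms. It comes from the noncentral t with 68 df, SE 0.382, and an upper 2.5% critical value of 1.995.

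| Transfused, control vs iron | Difference | Shift (points) | Share of the 1-point target | Chance of significance favouring iron |
|---|---|---|---|---|
| Equal | 0 | 0 | 0 | 2.5% |
| 38% vs 25% | 0.13 | 0.04 to 0.10 | 4 to 10% | 3.2 to 4.4% |
| 70% vs 24% | 0.46 | 0.14 to 0.35 | 14 to 35% | 5.5 to 14.2% |

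**Sensitivity to the assumptions.** With R from 2 to 4 and a total rise in red cells of 10 to 30%, the shifts are 0.02 to 0.12 points at 38% vs 25% and 0.08 to 0.43 points at 70% vs 24%. The picture is the same.

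**Direction.** The calculation holds the patients' own red cell mass equal in both arms. If iron raises it, the denominator grows in the iron arm and its percentage falls, which works against iron. The net sign is therefore not fixed.

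**The case against.** **Only one scale appears.** Effect, SD and reference difference are all in per cent, and the absolute difference in the Discussion can be read as percentage points. That makes the percentage the likely intention, and suspicion that the unit would be chosen after the data are seen would be speculation. What stands is that the sections defining and analysing the outcome never state the scale.

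**The transfusion gap may not arise.** The cited randomized trial found no overall difference in transfusion rates, and with equal rates the shift disappears. The 38% versus 25% figures are a conditional cost example and the one-third to two-thirds range is background literature; neither is a design assumption. The Discussion also says an effect on transfusion is likely only if iron affects erythropoiesis, so a 46-point gap sits badly with a null of equal production. All of this stands and limits the size.

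**Biased transfusion decisions.** A reader might infer that nurses who know the allocation would steer transfusion towards controls. The document does not support this as an expected bias: the treating team is blinded, and the indications for transfusion are listed.

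**Other measures are planned.** Haemoglobin change, transferrin receptor, patients transfused and units transfused will be reported by arm, so an imbalance would be visible. That helps a reader, but does not show how far the primary difference depends on the denominator.

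**Supporting analyses usually sit in the SAP.** True, and their absence from an article is no fault. The scale of the primary variable, however, is fixed in this document, and fixed loosely.

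**Conclusion.** The point holds as a minor one. The primary variable lacks a stated scale, the power statement covers only the percentage, and transfusion before day 7 can move that percentage without any change in red cell production.

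The movement is small: about 0.04 to 0.10 points at the cost illustration and zero with equal transfusion rates. It reaches about 0.35 points only at rates from a non-randomized comparison. These figures rest on the assumed day-7 percentage, the assumed rise per unit and equal native red cell mass, none of which the document gives.

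A reader might infer that a positive result could be produced by transfusion alone. The figures do not support that: even the largest shift is well below the 1-point target, and a larger red cell mass on iron would act the other way.

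**What to change.** 1. In Statistics, state that the primary variable is the reticulocyte percentage at day 7.
2. Reconcile this with the sample size section, which powers the maximum count. The text should not say that day 7 is what was powered.
3. Prespecify the absolute reticulocyte count at day 7 (percentage × red cell count from the same sample) as a supporting analysis by the same method.
4. Report it with its confidence interval beside the percentage and the transfusion rates by arm, and interpret a difference in percentage as increased erythropoiesis in the light of it.

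The full blood count is already collected daily for seven days, so the cost is one extra analysis. Treatment and transfusion practice are unaffected. The downside is that the two measures may disagree, which would have to be discussed. The document gives no effect or SD in cells per litre, so no power can be stated for the supporting analysis.

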### Definition of datasets analyzed

The safety set will comprise all randomized participants who receive at least one dose of the study drug or are randomized to standard care. The full analysis set will comprise all randomized participants for whom at least initial and day 7 reticulocyte counts are available. The per-protocol set will comprise all participants in the full analysis set who are deemed to have no major protocol violations that could interfere with the objectives of the study. Safety summaries will be performed on the safety set.

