#### ***Haematological measures***

As haematopoietic indices, full blood count and serum transferrin receptor concentrations will be measured. These will be collected daily for 7 days following admission. In addition, the number of patients requiring blood transfusion during hospital admission and the transfusion index (units/patient) will be determined.

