### Selection and withdrawal of participants

#### ***Recruitment***

Participants are identified by their presence on surgical lists and are recruited from the trauma wards. The investigator informs the participant or the participant’s nominated representative (other individual or other body with appropriate jurisdiction), of all aspects pertaining to participation in the study. Active participation in the study is for the first seven days of hospital admission. The study intervention is complete after the third day (administration of i.v. iron) with daily blood tests until day 7. The medical notes are reviewed following hospital discharge for in-hospital complications and medication use.

Participants are informed that entry into the trial is voluntary and that they are free to withdraw at any time without effect on subsequent care. Data on time to discharge and postoperative mortality are collected routinely and separately from this study. These outcome data are therefore available for all randomized participants.

Patients who are unable to provide consent for themselves are not included in this study, owing to its pilot nature and the off-label use of intravenous iron.

Patients for whom language may be a barrier are eligible for inclusion to the study using standard interpreting services. In practice, this is a very small proportion of the total older population in the study centre.

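### The full analysis set admits only patients with a day 7 count, and the safety set requires a dose in the iron arm only, so both arm comparisons can lose the protection of randomisation

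*Protocol article*

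**What the plan says.** Three sets are defined under Definition of datasets analyzed.

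- **Full analysis set:** "The full analysis set will comprise all randomized participants for whom at least initial and day 7 reticulocyte counts are available".
- **Per-protocol set:** nested inside it: "The per-protocol set will comprise all participants in the full analysis set who are deemed to have no major protocol violations".
- **Safety set:** "The safety set will comprise all randomized participants who receive at least one dose of the study drug or are randomized to standard care". Its use is then fixed: "Safety summaries will be performed on the safety set".

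The Statistics section ties the primary comparison to the first of these: "The primary outcome measure, difference in mean reticulocyte count between groups in the full analysis set will be analyzed". The test is an unpaired t test or its rank equivalent. The Discussion names day 7 as the primary time point.

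On available data, Laboratory analyses schedules blood samples on admission and once on each of days 1 to 7. Haematological measures says of the full blood count and transferrin receptor: "These will be collected daily for 7 days following admission". Recruitment says of time to discharge and postoperative mortality: "These outcome data are therefore available for all randomized participants".

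**The concern.** A full analysis set is meant to keep patients as randomised. This one is a day 7 completer set under that name. Entry depends on being alive, still under observation and sampled a week after admission, all of which follow allocation and could be affected by it. Patients who recover and leave early, and patients who die or withdraw, all drop out of the primary comparison.

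The safety set has a different fault. An iron patient who deteriorates or withdraws before the first infusion is removed, while the same patient in the control arm is kept. Any such removal that is linked to an adverse event makes iron look safer.

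The per-protocol set sits inside the full analysis set, and the safety set drops undosed iron patients. So no defined set is guaranteed to hold all randomised patients by allocated arm. The trial is a pilot whose result is to inform whether a full-scale trial follows, so the primary estimate should rest on the randomised groups.

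**Working it through.** **1. The plan's own figures.** From Sample size and justification: 40 per arm randomised, 35 per arm evaluable, difference 1.0%, SD 1.6%. The drop-out allowance is 10/80 = 12.5%, and 35/(1 − 0.125) = 40, so that step is consistent. The 80% power at 35 per arm does not reproduce with two-sided alpha 0.05 (assumed; the article states no alpha). The noncentral t gives:

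| Per arm with a day 7 count | Power |
|---|---|
| 40 | 78.8% |
| 35 | 73.2% |
| 32 (20% lost, assumed) | 69.2% |
| 30 (25% lost, assumed) | 66.3% |
| 28 (30% lost, assumed) | 63.2% |

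The gap between 80% and 73.2% at 35 per arm is a separate sample size matter. It is not caused by the set definition. The rows below 35 rest on loss rates that the documents do not give.

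**2. When the completer difference is biased.** Let m be the share of an arm without a day 7 count, and D how far the missing patients' mean lies below the observed patients' mean, taken as equal in both arms. The observed mean then exceeds the true arm mean by m × D, so

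bias = (m_iron − m_control) × D.

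- Equal m and equal D: bias 0.
- 20% v 5% missing, D = 0.5 / 1.0 / 1.6: 0.15 × D = 0.075 / 0.15 / 0.24 points.
- 30% v 10% missing, same D: 0.20 × D = 0.10 / 0.20 / 0.32 points.

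The sign follows who is missing. If the missing patients would have had higher counts, D is negative and the bias reverses. All these shares are assumptions.

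**3. Outcome-related leaving, simulated.** Assumptions: true difference 1.0, SD 1.6, about 20% of controls leave before day 7, and better responders leave earlier. Leaving depends on earlier counts, with a day 5 to day 7 correlation of 0.7 and a correlation with baseline of 0.4. As the strength of dependence rises from 0.3 through 0.5 to 0.7, the completer estimate is 0.98, 0.95 and 0.88. The bias is therefore about 0.02 to 0.12, towards no effect.

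**4. A harsher assumption, in closed form.** Let leaving depend directly on the day 7 value with correlation ρ. Write h(c) = φ(c)/Φ(c). With 20% of controls leaving, c = 0.842 and h = 0.350. In the iron arm the threshold becomes c − ρ × (1.0/1.6). The completer estimate is 1.0 + 1.6 × ρ × [0.350 − h(iron threshold)].

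- ρ = 0.3: h = 0.433, estimate 0.96.
- ρ = 0.5: h = 0.494, estimate 0.88.
- ρ = 0.7: h = 0.560, estimate 0.77.

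**5. Scale.** The standard error of the difference at 32 per arm is 1.6 × √(2/32) = 0.40, so each of these biases is smaller than one standard error.

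**6. Safety set.** With k undosed iron patients, the sets are (40 − k) v 40. Each one removed is 1/40 = 2.5% of the arm, with no matching removal among controls.

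**The case against.** Several points on the other side stand.

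- Randomization and blinding says the team deciding fitness for discharge is blinded, and the Discussion expects no clinically significant effect of iron on length of stay or mortality. Both reduce the risk of differential loss. They do not remove it, because patients and ward nurses know the allocation and patients may withdraw.
- A reader might infer that loss will exceed the 12.5% allowance. The documents do not say so. The Discussion's remark, "Prolonging the observation time also risks losing participants due to discharge", concerns observation beyond day 7 and is part of the reason for choosing day 7. It shows that discharge is a recognised route of loss, but it gives no rate.
- A reader might infer that the secondary continuous outcomes inherit this set because they are to be analysed similarly. That word most naturally refers to the tests. No set is named for them.
- A reader might infer that mortality and complications are tilted towards iron. Only safety summaries are assigned to the safety set. Complications and 30-day mortality are listed separately with no set named, and the article also promises to present all adverse events in full. Randomisation and the first dose are both due within 24 hours of admission, so the pre-dose window is short.
- The requirement for an initial count is less harmful because it concerns a baseline value.
- Daily reticulocyte counts are implied by the sampling schedule and by the sample size section's reference to a maximum count, but they are never stated outright.

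Missing-data sensitivity analyses are commonly left to an analysis plan. The definitions of the sets are not left open here: the article fixes them, and fixes them badly.

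**Conclusion.** The point holds in a limited form. As written, the primary comparison is restricted by a post-randomisation event. It loses the protection of randomisation if loss is related to outcome and differs by arm. It would go too far to say that the sets undo the randomisation: with equal and equally informative loss in both arms the bias is zero.

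The size cannot be read from the documents. Under the assumed dependence on earlier counts it is modest, about 0.02 to 0.12 points on a true 1.0 and towards no effect. It reaches 0.23 only if leaving is tied strongly and directly to the day 7 value itself. Other assumed patterns of differential loss can change its sign.

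The safety set is asymmetric on its face and the error favours iron, but few patients are likely to be affected. The primary-analysis half matters more.

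**What to change.** - **Full analysis set:** all randomised patients, by allocated arm.
- **Primary estimate:** the day 7 difference from a likelihood-based repeated-measures model using the admission count and every available post-admission reticulocyte count from the scheduled samples. If the admission count is modelled as a response with a common mean in both arms, patients with only that count stay in the model. Confirm that reticulocytes are measured on the daily samples.
- **Deaths:** state how deaths before day 7 are handled, since the model otherwise implies counts for patients who have died.
- **Supporting analyses:** report day 7 completers as supportive. They do not test missing at random, so add a sensitivity analysis that departs from it, for example by shifting the unobserved values differently by arm.
- **Safety and clinical outcomes:** compare adverse events, complications, transfusion and 30-day mortality in all randomised patients as allocated. Report infusion reactions separately in dosed patients.

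The cost is revised wording, slightly more modelling and a missing-at-random assumption for the main estimate. No extra samples are needed if reticulocytes are already counted on the scheduled bloods.
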